#### Statistical analysis

Statistical analysis will be conducted by an appointed statistician blinded to group allocation using R software (version 4.2.1; R Foundation). Intergroup comparisons of RSFC will be performed using the DAPBI toolbox. Normally distributed continuous variables will be reported as mean±standard deviation, while non-normally distributed data will be reported as median [P25 P75]. A *p*-value of <0.05(two-tailed) will be set as the significance level for all analyses.

The intention-to-Treat (ITT) protocol will be used for the analysis of all outcomes. The ITT population will include all participants who are randomized, regardless of treatment adherence or protocol deviations. The missing value will be handled using multiple imputations.

First, intergroup comparisons of demographic data (such as age, sex, and educational level), illness duration, estimated premorbid intelligence function, and PA will be conducted to examine comparability across the three groups. Categorical data will be analyzed using the χ^2^ test. Normally distributed continuous variables will be tested using one-way analysis of variance (ANOVA), whereas the non-normally distributed data will be analyzed using the Kruskal–Wallis test.

Analysis of covariance (ANCOVA) will be applied to the primary outcome and other cognitive measures, with age, estimated premorbid intelligence ability, and PA as covariates. ANCOVA with age and PA as covariates will be used for clinical measures and brain metabolites. Repeated measures ANOVA will be used to compare differences in hippocampal functional connectivity among the three groups. Age, sex, and years of education will be included as covariates. *Post hoc* analysis will be performed for RSFC with interaction effects. Multiple comparisons for hippocampal functional connectivity will be corrected using cluster-level family-wise error (FWE) correction, with a significance threshold set at a p-value of < 0.05. The χ2 test will be used to compare the rate of AEs and SAEs between the groups. Finally, Spearman correlation analysis will be performed to examine the relationships between cognitive outcome measures and imaging indicators exhibiting intergroup differences.

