#### Sample size calculation

The PASS software (version 21.0.3) was used to calculate the sample size. Based on two acupuncture trials that used the Symbol Digit Modalities Test (SDMT) as the primary outcome (56, 57), we estimated that the mean and standard deviation of the change in the SDMT score at week 8 after randomization would be 3.75 ± 4.95, 2.45 ± 5.21, and 1.30 ± 4.35 for the VA, SA, and waitlist control groups, respectively. With *α* = 0.05, *β* = 0.2, a power of 0.8, and a two-sided test for group differences, 36 participants are required in each group. Assuming a 20% dropout rate, 43 cases are needed per group, resulting in a total sample size of 129 participants.

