##### rs-fMRI data

The preprocessing of rs-fMRI data will be performed using the Statistical Parametric Mapping (SPM) 12 (Wellcome Trust Centre for Neuroimaging; http://www.fil.ion.ucl.ac.uk/spm) and the Data Processing and Analysis of Brain Imaging (DPABI) toolbox according to the following steps: (1) removal of the first 10 rs-fMRI images to allow for signal stabilization; (2) slice-timing correction; (3) realignment for head motion correction (excluding participants with head motion > 3 mm or head rotation > 3°);(4) normalization of functional images into Montreal Neurological Institute (MNI) space through the DARTEL alignment method and resampling to a voxel size of 3 × 3 × 3 mm^3^; (5) regression of nuisance covariates (including Friston-24 head motion parameters, global mean signals, white matter signals, and cerebrospinal fluid signals); (6) smoothing using a Gaussian kernel with a full width at half maximum (FWHM) of 6 mm; and (7) band-pass filtering (0.01–0.08 Hz) of the time series for each voxel to remove low-frequency drift and high-frequency noise.

The bilateral hippocampi will be selected as seed regions to perform seed-to-voxel RSFC analysis. These regions will be extracted from the Automated Anatomical Labeling (AAL) atlas. FC between each seed region and all other brain voxels (excluding the seed clusters) will be calculated using the DPABI toolbox. The mean time series of the left and right hippocampi will be extracted separately, and Pearson’s correlation coefficients will be calculated between the mean time series of each seed and the time series of all other voxels. The resulting correlation coefficients will then be *z*-normalized using Fisher’s *r*-to-*z* transformation. Finally, an RSFC map for each seed region will be generated for each participant.

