##### Secondary outcome measures

Cognitive measures include the following: Baseline-to-endpoint (week 8) changes in the Digit Span Forward Test (DST-F), the Trail Making Test Part A(TMT-A), immediate and delayed recall of the Rey Auditory Verbal Learning Test (RAVLT), copy trial, immediate and delayed recall of the Rey–Osterrieth complex figure test (RCFT),the Trail Making Test Part B(TMT-B), the Digit Span Backward Test (DST-B), the Stroop Color and Word Test (SCWT), the phonemic fluency test, the category fluency test, the action fluency test, and the 30-item Boston Naming Test (BNT-30).Imaging measures include the following: Changes in NAA, Cho, Glu, Gln, Lac, Ins, GPC, GSH, and RSFC of each hippocampus at week 8.Clinical symptoms and quality of life measures include the following: Baseline-to-endpoint (week 8) changes in the Multidimensional Fatigue Inventory (MFI-20), Pittsburgh Sleep Quality Index (PSQI), Generalized Anxiety Disorder 7-item scale (GAD-7), 24-item Hamilton Depression Scale (HAMD-24), and 36-Item Short Form Survey (SF-36).

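### Hippocampal connectivity is promised an ITT analysis with imputation, but the motion exclusion and the voxelwise repeated-measures ANOVA show no way to score every randomised patient

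*Protocol article*

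**What the plan says.** The Statistical analysis section of the protocol article makes three general statements with no exception for imaging. The first sets the principle: "The intention-to-Treat (ITT) protocol will be used for the analysis of all outcomes". The second fixes who belongs to that set: "The ITT population will include all participants who are randomized, regardless of treatment adherence or protocol deviations". The third deals with gaps in the data: "The missing value will be handled using multiple imputations".

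The Secondary outcome measures section lists, among the imaging measures, change in "RSFC of each hippocampus at week 8". RSFC is therefore covered by the general statements.

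The rs-fMRI data section builds this outcome as a map: "FC between each seed region and all other brain voxels" is computed for each participant. Its realignment step carries a quality rule, "excluding participants with head motion > 3 mm or head rotation > 3" (degrees).

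For the comparison, Statistical analysis states: "Repeated measures ANOVA will be used to compare differences in hippocampal functional connectivity among the three groups". This is done in an imaging toolbox rather than in R, with cluster-level family-wise error (FWE) correction.

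The only planning figure for loss is in Sample size calculation: "Assuming a 20% dropout rate, 43 cases are needed per group". It was set for the Symbol Digit Modalities Test (SDMT), the primary outcome. No rate of motion failure or missing scans is given.

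**The concern.** Two populations are stated for one endpoint. The general rule keeps every randomised patient and imputes what is missing. The imaging rule takes the participant out, and someone who is excluded is not imputed. Because one of the two scans falls at week 8, the exclusion can depend on an event after randomisation.

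The outcome is also a whole-brain map for each seed, not a single value, and a two-visit repeated-measures ANOVA in its usual form compares paired maps. The article does not say how the stated imputation would supply a map.

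At stake is what the RSFC result means. Staying to week 8 and lying still at week 8 could differ by arm: the waitlist arm is not blinded, and its patients may be advised to withdraw if worsened symptoms do not improve. Imaging indicators that differ between groups are then carried into the correlation with cognition. The mechanism finding could therefore rest on a selected subset that readers are told is the ITT population.

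**Working it through.** **1. The plan's own figures.** 36 × 1.2 = 43.2, stated as 43 per arm, and 3 × 43 = 129. A 20% loss from 43 leaves 43 × 0.80 = 34.4, not 36. The loss that takes 43 to 36 is 1 − 36/43 = 16.3%. So 20% is a planning assumption for SDMT, not a measured rate of scan loss.

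**2. Patients with two usable scans.** Let d be dropout before the week-8 scan and m the motion failure per scan. The value of m is an assumption, taken as independent between visits. The proportion with a usable pair is (1 − d)(1 − m)².

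| d | m | pairs per arm | pairs of 129 | without a pair |
|---|---|---|---|---|
| 20% | 0 | 34.4 | 103 | 20% |
| 20% | 5% | 31.0 | 93 | 28% |
| 20% | 10% | 27.9 | 84 | 35% |
| 20% | 15% | 24.9 | 75 | 42% |
| 16.3% | 0 | 36.0 | 108 | 16% |
| 10% | 5% | 34.9 | 105 | 19% |
| 5% | 5% | 36.9 | 111 | 14% |

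The first row is dropout alone: 129 × 0.20 = 25.8, about 26 patients.

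**3. What another model would gain.** Assume equal variance at both visits and scan-rescan correlation r = 0.5 (range 0.3 to 0.7). Neither comes from the article. With two visits, the arm-by-time test is a test of change in complete pairs.

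- Variance per pair for change is 2(1 − r). With a common baseline mean (baseline adjustment) it is 1 − r². The ratio of standard errors is √[(1 − r²) / (2(1 − r))] = √[(1 + r)/2].
- This gives 0.806, 0.866 and 0.922 at r = 0.3, 0.5 and 0.7. The standard error falls by 19%, 13% and 8% in the same complete pairs.
- Baseline-only scans of dropouts inform only the common baseline mean, which cancels between arms. With m = 0 the further ratio is exactly 1, so they add nothing.
- Week-8-only scans do add. Their number relative to pairs is m/(1 − m), and the further ratio is 1/√[1 + (1 − r²)m/(1 − m)].
- At r = 0.5 that is 0.981, 0.961 and 0.940 for m = 5%, 10% and 15%: a further 1.9%, 3.9% and 6.0%. The extremes over the grid are 1.3% (r = 0.7, m = 5%) and 7.2% (r = 0.3, m = 15%).
- Combined at r = 0.5: 0.866 × 0.981 = 0.85, 0.866 × 0.961 = 0.83 and 0.866 × 0.940 = 0.81.

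**The case against.** The strongest reply is that a journal article condenses. It promises imputation without exception, and the way maps, or values extracted from clusters, would be imputed may stand in a full protocol or analysis plan that is not shown. The motion rule is a parenthesis in a preprocessing step that also serves healthy controls, who are scanned once, so its reference to participants may be generic quality-control wording. RSFC is secondary, the mechanism aim is exploratory, and the SDMT result is untouched.

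Much of this stands, and it rules out several stronger readings:

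- **That only patients with two usable scans can be scored.** The article shows no other route, but it does not exclude one.
- **That at least 20% will be lost.** The 20% is an assumption for another outcome, and lower dropout can give a smaller loss.
- **That one failed scan certainly discards the patient's good scan.** This is the literal reading, but the case is not spelled out.
- **That exclusion is known to differ by arm.** Baseline assessment comes before allocation, so baseline motion cannot be caused by arm. Differential loss at week 8 is possible, but no size or direction can be given.
- **That recovering single scans brings a 15–19% gain in precision.** At r = 0.5, about 13 of those points come from handling the baseline and have nothing to do with the analysis population.

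What the reply does not remove is the conflict in stated text. A fuller plan could add an imputation method, but it could not make it true both that every randomised patient is analysed and that some are excluded for motion.

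**Conclusion.** The concern holds as a contradiction about the RSFC population. Followed as written, the result would in practice describe patients with usable scans but carry an ITT label.

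The size is conditional. About 26 of 129 patients would lack a week-8 scan if the planned dropout occurs. Between 28% and 42% would lack two usable scans if motion failure is also 5–15% per scan. The figure is 14% at 5% dropout and 5% motion failure. The motion rates and their independence between visits are assumptions.

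A reader might infer that a mixed model would restore an ITT analysis. It would not: selection by dropout remains, because a dropout's baseline map adds nothing to the between-arm contrast. The gain in precision is real but separate, about 13% (8–19%) from baseline handling and a further 2–6% (1–7%) from week-8-only scans. The primary outcome is not affected.

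**What to change.** In Statistical analysis, exempt RSFC from the ITT-with-imputation statement. Define its set as randomised patients with usable scans, analysed in the arm assigned, and label the result an available-scan analysis. Imputation can stay for outcomes that are single values.

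In the rs-fMRI data section, apply the motion rule to the scan rather than the participant. The spectroscopy quality rule is already worded in this way, at the level of the spectrum.

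Report missing and unusable scans by arm and visit.

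Replace the repeated-measures ANOVA by a model with a common baseline mean, keeping the cluster-level FWE correction. A voxelwise mixed model lets week-8-only scans contribute. Baseline-adjusted week-8 maps are the simpler option and keep most of the gain.

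No new patients or data are needed. The costs are wording changes, more analysis work, possibly another imaging package, reliance on missing-at-random for lost scans, and loss of the ITT label for this secondary endpoint. The changes should be made before the groups are unblinded.

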## Methods and analysis

### Study design

This is a prospective, three-armed randomized controlled trial using rs-fMRI and ^1^H-MRS, which will be jointly conducted by two hospitals in Chengdu. A total of 129 patients with ME/CFS occurring after COVID-19 and 30 HCs who have fully recovered from COVID-19 will be recruited. After baseline assessment, eligible patients will be randomly assigned to a verum acupuncture (VA), sham acupuncture (SA), or waitlist control group in a 1:1:1 ratio and will receive an 8-week intervention or wait. Figure 1 shows the flow chart of this trial. This study will be conducted in accordance with the Declaration of Helsinki, the Consolidated Standards of Reporting Trials (CONSORT) guidelines (50), and the Revised Standards for Reporting Interventions in Clinical Trials of Acupuncture (STRICTA) guidelines (51). This protocol has been reviewed and approved by the Ethics Committees of the Affiliated Hospital of Chengdu University of Traditional Chinese Medicine and the Public Health Clinical Center of Chengdu and has been registered at ClinicalTrials.gov (NCT07357688).

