#### Randomization and blinding

An appointed investigator who is not involved in participant recruitment, treatment, outcome assessment, or data analysis will generate the random sequence using SAS version 9.4 (SAS Institute, Inc) through a simple randomization method. The acupuncturist, who will not be involved in participant recruitment, will receive the grouping information for each participant from this investigator via short message service (SMS).

Participants in the VA and SA groups will be blinded to treatment allocation. VA and SA treatments will be performed in separate treatment rooms to reduce the risk of accidental unblinding. Participant recruitment, outcome assessment, imaging processing, and data collection, management, and analysis will be performed by independent investigators. The VA, SA, and waitlist control groups will be coded as A, B, and C, respectively, throughout the trial period until the completion of the primary analysis to ensure concealment of treatment assignment. It will be difficult to blind participants in the waitlist control group because they will not receive treatment immediately. A participant’s treatment allocation will be unblinded in the event of SAEs occurring during the trial.

The success of blinding will be evaluated for participants in the VA and SA groups at two time points (the first week and the 8th week after treatment) by asking them to guess their group allocation. The Bang’s blinding index (Bang’s BI) will be calculated according to the guessed proportion of each arm (52, 53).

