#### Outcomes

##### Primary outcome measure

The primary outcome is the change from baseline to week 8 in the SDMT score.

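### The ANCOVAs on change from baseline omit the outcome's own baseline value, so baseline is corrected only with a fixed slope of 1 and precision is given away

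*Protocol article*

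**What the plan says.** Protocol article, Primary outcome measure: "The primary outcome is the change from baseline to week 8 in the SDMT score". The Secondary outcome measures section also defines the cognitive, clinical and metabolite outcomes as changes, so each is measured at baseline.

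Protocol article, Statistical analysis: ANCOVA "will be applied to the primary outcome and other cognitive measures, with age, estimated premorbid intelligence ability, and PA as covariates". For the rest, "ANCOVA with age and PA as covariates will be used for clinical measures and brain metabolites". No other section adds the baseline value of the outcome to these lists. Hippocampal connectivity is analysed by repeated measures ANOVA and is not part of this point.

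The baseline comparison of the arms covers demographic data, "illness duration, estimated premorbid intelligence function, and PA will be conducted to examine comparability across the three groups"; baseline SDMT is not named there.

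Protocol article, Randomization and blinding: the sequence is generated "through a simple randomization method", and no stratification or minimisation is described.

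**The concern.** Subtracting baseline assumes that a one-point difference at baseline carries through as a full one-point difference at week 8. Whenever the within-arm regression of week 8 on baseline has a slope below 1, subtraction over-corrects, and an arm that happens to start low appears to improve more. ANCOVA on the baseline value estimates that slope from the data.

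Simple randomisation with about 43 per arm does nothing to limit chance differences in baseline SDMT. Age and premorbid intelligence may stand in for baseline SDMT in part, but the score itself is already collected. At stake is precision on the primary contrast, including verum against sham, where the planned difference is only 1.30 points.

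The covariates are written out model by model. A statistician who follows the text would leave baseline out, so this is a stated choice and not a detail left to a fuller plan.

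**Working it through.** **Inputs from the documents.** Sample size calculation: mean and SD of SDMT change "3.75 ± 4.95, 2.45 ± 5.21, and 1.30 ± 4.35 for the VA, SA, and waitlist control groups, respectively"; 43 per arm randomised. Planned verum minus sham difference: 3.75 − 2.45 = 1.30.

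**Input assumed.** The baseline to week-8 correlation r is not given. The range 0.5 to 0.9 is used, with equal SD s at both times and no other covariates in the model.

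**The plan's own figure.** The sample size section states "a power of 0.8, and a two-sided test for group differences, 36 participants are required in each group". This does not reproduce from its inputs. The SD of the three means is 1.001 and f = 1.001/4.85 = 0.206; a three-group F test then needs 77 per group for 80% power, and power at 36 is 45.8%. That is a separate matter. Only the SDs and the 1.30 are used below.

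**Step 1, pooled SD of change.** √[(4.95² + 5.21² + 4.35²)/3] = √(70.57/3) = √23.52 = 4.85.

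**Step 2, variances.**
- Change score: 2s²(1 − r)
- Baseline-adjusted: s²(1 − r²)
- Ratio, adjusted to change score: (1 + r)/2

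**Step 3, the same effect seen conditionally.** Given the observed baselines, the change-score contrast is shifted by −(1 − r) × (baseline difference between the arms). The implied baseline SD is s = 4.85/√[2(1 − r)]. For a 0.3 SD imbalance the size of the shift is (1 − r) × 0.3 × s. At r = 0.7: s = 4.85/√0.6 = 6.26, and 0.3 × 0.3 × 6.26 = 0.56.

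**Step 4, scale for the shift.** The standard error of a two-arm change contrast at 43 per arm is 4.85 × √(2/43) = 1.05.

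| r | s | Adjusted / change variance | Adjusted lower by | Change score higher by | Shift at 0.3 SD | Shift / SE | Shift / 1.30 |
|---|---|---|---|---|---|---|---|
| 0.5 | 4.85 | 0.75 | 25% | 33% | 0.73 | 0.70 | 56% |
| 0.7 | 6.26 | 0.85 | 15% | 18% | 0.56 | 0.54 | 43% |
| 0.8 | 7.67 | 0.90 | 10% | 11% | 0.46 | 0.44 | 35% |
| 0.9 | 10.85 | 0.95 | 5% | 5% | 0.33 | 0.31 | 25% |

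With baseline in the model, 36 evaluable participants per arm would be worth 36/0.75 = 48 (r = 0.5) down to 36/0.95 = 37.9 (r = 0.9) in the change-score analysis.

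**Step 5, how likely a 0.3 SD imbalance is.** The standard error of the baseline difference is √(2/43) = 0.216 SD, so 0.3 SD is 1.4 standard errors, and a given pair of arms exceeds it with probability about 0.16.

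**Step 6, one effect or two.** The variance difference is 2s²(1 − r) − s²(1 − r²) = s²(1 − r)², which is exactly the variance of the (1 − r) × imbalance term. At r = 0.7: (0.3 × 6.26)² = 3.5 out of 23.5, the same 15%. Steps 2 and 3 describe a single loss.

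**The case against.** The stated analysis is a legitimate one. A change score does use baseline. Over repeated randomisations its contrast is unbiased, and its test is valid. This stands, and it limits the point to efficiency.

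A reader might infer that chance imbalance goes uncorrected. The documents do not support that: the outcome is a change, so imbalance is corrected with slope 1, and only (1 − r) of it remains. At r = 0.7 a 0.3 SD imbalance is 1.88 points, of which 0.56 is left.

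A reader might also add conditional bias to lost precision as a second harm. Step 6 shows they are the same quantity. The shift is already inside the standard error of 1.05, and it is as likely to favour one arm as the other. Setting it against 1.30 without showing that standard error makes it look larger than it is.

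The size is uncertain. No value of r is given, about 84% of trials would show less than a 0.3 SD imbalance between a given pair of arms, and (1 + r)/2 describes a model without other covariates. The gain over the listed covariates cannot be derived from the documents. All of this stands. It does not remove the omission, and the remedy uses a measurement already taken.

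**Conclusion.** The point holds as a matter of efficiency. The stated ANCOVAs leave out the outcome's own baseline value. For r from 0.5 to 0.9 the residual variance is about 33% to 5% higher than with baseline adjustment. This rests on an assumed r, equal variances, and no allowance for what age, premorbid intelligence and PA already explain.

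It does not amount to an invalid primary analysis or an inflated type I error, and nothing in the outcome and analysis sections is contradictory here. Nor should it take weight from the sample size: at 36 per group, adding baseline moves the power of the three-group F test from 45.8% to between 58.1% (r = 0.5) and 47.8% (r = 0.9), so it does not restore 80%. How baseline enters the multiple imputation is a detail the article may leave to the full plan, and is not part of this point.

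Severity: should be fixed, as a free improvement.

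**What to change.** Pre-specify the baseline value of the same measure as a covariate in each ANCOVA: baseline SDMT for the primary outcome, and each measure's own baseline value for the other cognitive, clinical and metabolite outcomes. With baseline in the model, change and week-8 score give the same treatment estimate, so the endpoint definition can stay.

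The cost is one covariate and one degree of freedom per model, with no new data and no added participants. The change should be written down before unblinding, because adding baseline after an imbalance has been seen would be a data-driven choice.

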Currently, there is no known cure for ME/CFS, and a symptomatic intervention is the main principle for the treatment of this syndrome. An array of strategies has been proposed for the management of ME/CFS, such as activity management, non-steroidal anti-inflammatory drugs (NSAIDs), antipsychotics, anticonvulsants, narcotics, and antidepressants (33, 34). However, these treatments primarily target non-cognitive symptoms such as fatigue, PEM, sleep disturbance, and pain, while their effects on cognitive problems are minimal (35). The efficacy of other approaches, such as immunoregulators, energy therapy, vitamin supplements, and dietary therapy for ME/CFS, is unclear due to limited and mixed findings (12, 36).

Acupuncture is an important complementary and alternative therapy for ME/CFS. The results of a meta-analysis showed that acupuncture could significantly improve fatigue, pain, depression symptoms, and quality of life in patients with ME/CFS compared to placebo controls, whether used alone or in combination with moxibustion or rehabilitation (37–39). However, research focused on the impact of acupuncture on cognitive function in ME/CFS is limited (38), despite evidence that acupuncture treatment can significantly improve cognitive dysfunction caused by neurological or neuropsychiatric disorders such as mild cognitive impairment (MCI), stroke, and insomnia (40–42). In addition, no one has evaluated the effect of acupuncture on cognitive function in PCME/CFS.

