#### Physical activity monitoring

Physical activity (PA) is a major factor that triggers the exacerbation of symptoms in patients with ME/CFS. To control the influence of variation in PA on study results, accelerometer-based PA monitoring will be performed. All participants will be instructed to wear an ActiGraph wGT3X-BT accelerometer (ActiGraph LLC, Pensacola, FL, USA) on the left wrist at all times throughout the 8-week trial period, except during sleep or water-based activities such as showering and swimming. Moreover, two appointed investigators will contact participants through WeChat (a social media platform in China) video calls between 8:30 a.m. and 9:00 a.m. each day to ensure adherence. The accelerometer-collected data will be exported every 2 weeks.

ActiLife version 6.13.4(ActiGraph Corporation) will be used to download and analyze the accelerometer data. The raw data will be converted into counts of movement using 60-s epoch lengths(ct/min). Non-wear time will be defined as zero accelerometer counts for any continuous 90 min. A day will be considered valid if the wear time is ≥ 10 h. Summary measures will be calculated using the average values across all valid days, including total PA time (min/day >100 ct/min), sedentary time (min/day for ≤100 ct/min), light PA time (min/day for 100–2019 ct/min), moderate PA time (min/day for 2020–5,998 ct/min), and vigorous PA time (min/day for ≥5,999 ct/min).

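### The primary ANCOVA adjusts for physical activity averaged over the 8 weeks after randomisation, which can remove, inflate or distort the effect of assignment

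*Protocol article*

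**What the plan says.** The endpoint is plain: "The primary outcome is the change from baseline to week 8 in the SDMT score". Under Statistical analysis, it and the other cognitive measures are analysed by ANCOVA "with age, estimated premorbid intelligence ability, and PA as covariates". Clinical measures and brain metabolites are analysed by ANCOVA with age and PA. The functional connectivity model does not include PA. The same section declares an intention-to-treat analysis for all outcomes.

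PA is defined under Physical activity monitoring. The device is worn "on the left wrist at all times throughout the 8-week trial period", and "Summary measures will be calculated using the average values across all valid days". The reason given is: "To control the influence of variation in PA on study results, accelerometer-based PA monitoring will be performed". No wear period before randomisation and no baseline PA value is described.

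Study design fixes the order: "After baseline assessment, eligible patients will be randomly assigned", and the 8 weeks of intervention or waiting follow.

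PA is also listed with patient characteristics: comparisons of demographic data, "illness duration, estimated premorbid intelligence function, and PA will be conducted to examine comparability across the three groups".

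**The concern.** A covariate in a randomised comparison should be fixed before assignment. If assignment can change it, the adjusted contrast is no longer the total effect of being assigned, which is what an intention-to-treat analysis is meant to estimate.

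The article itself supplies reasons why PA could be affected:

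- The Introduction reports that "acupuncture could significantly improve fatigue, pain, depression symptoms, and quality of life in patients with ME/CFS". Less fatigue could change how active patients are. This route is open in every contrast.
- Both acupuncture arms attend 24 outpatient sessions, while the waitlist arm has weekly telephone follow-up. This route is open only in contrasts with waitlist.
- Physical activity monitoring names activity as a main trigger of worsening symptoms, which ties PA to outcome.

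If PA carries part of the treatment effect, adjustment takes that part out or, with opposite signs, adds to the estimate. If PA and SDMT change share an unmeasured cause, such as general health, adjustment can create a difference where none exists. A larger sample does not cure either problem.

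The comparability check has the same fault. A between-arm difference in an on-treatment average may itself be a treatment effect, and similar averages do not show that the arms started alike.

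**Working it through.** **Timing.** Baseline assessment comes first, then randomisation, then 8 weeks of treatment or waiting. PA is the average over those 8 weeks. As written, the covariate is measured after randomisation.

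**Inputs from the documents** (Sample size calculation). Planned SDMT changes are 3.75 (SD 4.95) for verum, 2.45 (SD 5.21) for sham and 1.30 (SD 4.35) for waitlist, with 43 randomised per arm.

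- Verum minus sham: 3.75 − 2.45 = 1.30.
- Verum minus waitlist: 3.75 − 1.30 = 2.45.
- Pooled SD: √[(4.95² + 5.21² + 4.35²)/3] = 4.85.

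**Inputs that are assumed.** The documents give no figure for either of these:

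- a, the between-arm shift in mean 8-week PA, in SD units: 0 to 0.5 in absolute value.
- r, the within-arm correlation of PA with SDMT change: up to 0.4 in absolute value.

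**Formula.** Adjusted contrast = total contrast − a × r × SD.

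| Size of a | Size of r | Movement (points) | Share of 1.30 | Share of 2.45 | Verum-sham, same sign | Verum-sham, opposite signs |
|---|---|---|---|---|---|---|
| 0 | any | 0 | 0% | 0% | 1.30 | 1.30 |
| 0.2 | 0.2 | 0.2 × 0.2 × 4.85 = 0.19 | 15% | 8% | 1.11 | 1.49 |
| 0.3 | 0.3 | 0.3 × 0.3 × 4.85 = 0.44 | 34% | 18% | 0.86 | 1.74 |
| 0.5 | 0.4 | 0.5 × 0.4 × 4.85 = 0.97 | 75% | 40% | 0.33 | 2.27 |

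**Check by simulation.** With 4,000 runs, 43 per arm, a = r = 0.3 and the verum-sham SD √[(4.95² + 5.21²)/2] = 5.08, the mean estimate was 1.29 unadjusted and 0.84 adjusted. The formula with that SD gives 1.30 − 0.3 × 0.3 × 5.08 = 0.84.

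**Null case with a common cause.** Suppose treatment has no effect on SDMT, PA shifts by 0.3 SD, and an unmeasured factor loads 0.55 on both PA and SDMT change.

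- Within-arm correlation: 0.55 × 0.55 = 0.30.
- Expected adjusted estimate: −0.3 × 0.30 × 4.85 = −0.44. Simulation gave −0.45, with a two-sided rejection rate of 7.0%.
- Direction: the standard error is about 1.0 point (4.85 × √(2/43) = 1.05, a little less after adjustment). The upper tail is then Φ(−1.96 − 0.45) ≈ 0.8%, and the lower tail is Φ(−1.96 + 0.45) ≈ 6.6%.

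Nearly all the excess error therefore runs against acupuncture. With opposite signs it would run in favour. In a stronger version (shift 0.5 SD, loading 0.5 on each, SD 5.08) simulation gave −0.66 and 9.6% rejection, against 5.1% unadjusted.

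**The case against.** The strongest reply is that no passage shows acupuncture changing activity. The cited evidence concerns fatigue, pain, mood and quality of life. If treatment leaves PA unchanged, the bias is zero and PA merely explains some variance. That stands, so a reader who infers that adjustment certainly removes part of the effect goes further than the documents allow. What they support is that it can.

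Four further limits also stand:

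- A reader might infer that clinic attendance separates all three arms. Verum and sham share the same session schedule, so attendance bears only on contrasts with waitlist. For verum versus sham the argument rests on the unquantified route from symptoms to activity. Nor do the documents say how active waitlist patients will be.
- A reader might take 75% as an expected loss. It is the extreme corner of an assumed range. Because the article links activity to symptom worsening, the correlation could be negative, and adjustment could then enlarge the estimate.
- A reader might take the 7% error rate as a risk of false claims of efficacy. In that scenario the error lies mostly in the opposite tail.
- Listing PA among comparability variables would fit a baseline value defined in a fuller document that is not shown. The monitoring section describes no such value and states the aim of controlling for variation in PA, so this softens the point without answering it.

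The aim of controlling for activity is reasonable in itself. It does not justify conditioning the primary estimate on a variable that assignment may change.

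**Conclusion.** The point holds in this form: following the article as written conditions the primary SDMT comparison, and the other cognitive, clinical and metabolite comparisons, on a variable measured after randomisation that treatment can affect. The resulting contrasts need not equal the intention-to-treat effect that the plan declares. The comparability test on the same variable cannot show baseline balance.

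Neither the size nor the sign of the bias can be derived from the documents. Under the assumed ranges the verum-sham estimate moves by 0 to about 0.97 points, in either direction, against a planned difference of 1.30. The verum-waitlist estimate moves by up to 40% of 2.45. The conclusion that the covariate is badly chosen rests on its timing alone and does not depend on those assumptions. It should be corrected before analysis because it sits in the primary model.

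**What to change.** - Restrict the primary and secondary ANCOVAs to covariates fixed before randomisation.
- Remove trial-period PA from the comparability comparison.
- If adjustment for activity is wanted, take PA from a short pre-randomisation wear period with the same device, and use that value both as covariate and for comparability.
- Report trial-period PA by arm, labelled as a post-randomisation variable. Keep the PA-adjusted model only as a labelled exploratory or sensitivity analysis.

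The cost is a change of wording and, optionally, a few days of device wear before randomisation. The sample size of 129 need not change on this account. The downside is losing whatever outcome variance trial-period PA would have explained; a pre-randomisation PA value could recover part of it.
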